# Effectiveness of the YourCall™ text message intervention to reduce harmful drinking in patients discharged from trauma wards: protocol for a randomised controlled trial

**DOI:** 10.1186/s12889-016-3967-z

**Published:** 2017-01-09

**Keywords:** Alcohol use, Text messaging, Wounds and injuries, Brief intervention, Motivational interviewing, Trauma centers, Mobile health

## Abstract

**Background:**

Behavioural brief interventions (BI) can support people to reduce harmful drinking but multiple barriers impede the delivery and equitable access to these. To address this challenge, we developed YourCall™, a novel short message service (SMS) text message intervention incorporating BI principles. This protocol describes a trial evaluating the effectiveness of YourCall™ (compared to usual care) in reducing hazardous drinking and alcohol related harm among injured adults who received in-patient care.

**Methods/design:**

Participants recruited to this single-blind randomised controlled trial comprised patients aged 16-69 years in three trauma-admitting hospitals in Auckland, New Zealand. Those who screened positive for moderately hazardous drinking were randomly assigned by computer to usual care (control group) or the intervention. The latter comprised 16 informational and motivational text messages delivered using an automated system over the four weeks following discharge. The primary outcome is the difference in mean AUDIT-C score between the intervention and control groups at 3 months, with the maintenance of the effect examined at 6 and 12 months follow-up. Secondary outcomes comprised the health and social impacts of heavy drinking ascertained through a web-survey at 12 months, and further injuries identified through probabilistic linkage to national databases on accident insurance, hospital discharges, and mortality. Research staff evaluating outcomes were blinded to allocation. Intention-to-treat analyses will include assessment of interactions based on ethnicity (Māori compared with non-Māori).

**Discussion:**

If found to be effective, this mobile health strategy has the potential to overcome current barriers to implementing equitably accessible interventions that can reduce harmful drinking.

**Trial registration:**

Universal Trial Number (UTN) U1111-1134-0028. ACTRN12612001220853. Submitted 8 November 2012 (date of enrolment of first participant); Version 1 registration confirmed 19 November 2012. Retrospectively registered.

## Background

Alcohol misuse is a leading cause of premature death and disability in New Zealand incurring substantial costs to society and health services [1]. A multi-country study found the proportion of Emergency Department visits associated with alcohol use to be particularly high in New Zealand [2]. Injury is the largest contributor to alcohol-related mortality [1, 3] and alcohol is widely acknowledged as the leading risk factor for injury [1, 3]. Can a mobile health intervention reduce the recognised excess risk of ongoing harm and injury recurrence [4, 5] experienced by patients with hazardous drinking patterns discharged from trauma wards?

The imperatives to scale up population-based strategies to reduce alcohol-related harm are obvious. The most effective among these include increasing the minimum purchasing price and age, reducing availability and access, and restricting advertising and other promotions of alcohol [6, 7]. However, these efforts are challenged directly and indirectly by the industry with capitulation to commercial interests a high risk in many countries [8]. Targeted interventions in clinical settings as a complementary approach can, at least partly, mitigate risks of on-going harm in contexts where the prevalence of alcohol problems is high.

The World Health Organization, the U.S. Substance Abuse and Mental Health Services Administration, and the U.S. Preventive Services Task Force, among other agencies advocate point-of-care opportunistic screening and brief interventions (BIs) to reduce risks of on-going harm [9–11]. The U.S. National Commission on Prevention Priorities ranks this approach to be among the five most effective clinical preventive services [12]. Screening and BIs for harm aim to identify a real or potential alcohol use problem and motivate an individual to lower their risk for alcohol-related problems [13, 14]. Drawing on a variety of behaviour change theories, these interventions employ three common strategies: 1) giving information or feedback, 2) understanding patients’ views of drinking and enhancing motivation, and 3) giving advice and negotiating responsive behaviour change [14].

A robust body of research indicates that screening and BIs in trauma care settings can reduce alcohol intake and lower levels of hospital re-attendance [6, 15]. However, such interventions are infrequently implemented in New Zealand [16]. In the U.S., despite screening and interventions for alcohol-related disorders being required for trauma centre accreditation [10] with related recommendations in the U.S. Trauma Service Guidelines [14], many centres fall short of the intended goals [17–19]. A 2011 U.S. state-based behavioural risk factor survey found fewer than one in six U.S. adults report ever discussing alcohol use with a doctor or other health professional; and two-thirds (65.1%) of those who report binge drinking 10 times or more in the previous month deny ever having this conversation [20].

Barriers to screening and intervention commonly proffered by health professionals include the lack of time, resources, training and workforce capacity; self-efficacy; discomfort discussing the topic; perceived difficulties interacting with patients who use substances; anticipated patient resistance; and scepticism about the likely benefits [16–19, 21]. Regardless of the explanation, the deficiencies encountered correspond to an important gap in quality of care. This is particularly unfortunate as trauma patients indicate they want healthcare teams to address their problems with alcohol [18, 22]. Furthermore, unlike many other harms with longer lead times, injury risks respond relatively rapidly to changes in drinking. However, the half-life of ‘teachable moments’ may be short and the risks of inequitable, delayed or poor access to standard referral pathways for alcohol misuse problems are high [23].

Social determinants can strongly influence alcohol use with more impoverished groups at significantly greater risk of experiencing related harms [24–26]. This is of particular concern in New Zealand, where Māori (indigenous people) have disproportionately high rates of injury and less access to health and rehabilitation services compared with non-Māori [27]. These are symbolic of significant breaches of the principles of partnership, participation and protection that underpin the relationship between the Government and Māori with respect to the founding document of Aotearoa New Zealand, Te Tiriti o Waitangi (The Treaty of Waitangi).

YourCall™ is a novel SMS-text message intervention designed to address the challenges noted above. The overall goal is to reduce hazardous drinking and alcohol-related harm among adults admitted to hospital following an injury and facilitate equitable benefits for Māori relative to non-Māori.

### Rationale for the intervention mode

It is argued that ‘mHealth (mobile health) technologies have the potential to change every aspect of the health care environment and to do so while delivering better outcomes and substantially lowering costs’ [28]. The vast majority of mHealth interventions tested to date have focused on chronic care management (e.g., diabetes and asthma), and health behaviours such as physical activity, obesity prevention and smoking cessation [28, 29].

To achieve our intended goal of supporting the reduction of hazardous drinking, we developed the YourCall™ intervention drawing on the extensive experience of members of the research team in designing and evaluating a range of mHealth interventions [30–34]. We commenced the process with a robust consultation process and feasibility study affirming the interest and acceptability of this approach among trauma patients [23]. As published in this journal previously [35], we then used a formal intervention development format to design, pre-test and refine a tailored suite of 16 text messages to be delivered over a four-week period after injury patients were discharged from hospital. The intervention development team included injury prevention practitioners, Māori and Pacific researchers, emergency and trauma service providers, substance use treatment providers, community stakeholders, and experts in mobile health technology. Our previous publication provides detailed information on the consultation process and feedback, the underpinning theory, development and final content of the intervention [35].

This paper describes the study design, baseline and outcome data collection procedures, and approach to analyses in the single-blind randomised controlled trial evaluating the effectiveness of the YourCall™ intervention in Auckland, New Zealand. The project is ongoing with the current stage involving collection of the final phase of secondary outcome data, and the analysis and presentation of the primary outcome data.

## Methods/design

### Design and hypothesis

The YourCall™ study is a two-group, parallel, single-blind randomised controlled-trial. Individuals who screened positive for hazardous drinking (Alcohol Use Disorders Identification Test [AUDIT] score 7-15 for females, 8-15 for males) were individually randomised to an intervention group or a usual care group (control) in a 1:1 allocation ratio (Fig. 1). We hypothesise that in comparison to hazardous drinkers discharged following an injury admission who received usual care (control group), those who received a structured sequence of SMS-text messages (YourCall™) incorporating brief intervention from harm principles:

**Fig. 1 Fig1:**
[figure not shown]
CONSORT diagram for YourCall™ trial

Will have reduced hazardous drinking at 3, 6 and 12 months follow-up as assessed by the AUDIT-C score (primary outcome at 3 months)Will have fewer subsequent medically attended injuries (identified through record linkage to national databases), andWill experience less adverse health and social outcomes, e.g., sexual harm, mental health problems, and legal consequences of heavy drinking (identified through a self-report survey at 12-months follow-up).

We also hypothesise that the effectiveness of the intervention (as measured above) will be similar among Māori and non-Māori.

### Participant recruitment and eligibility criteria

Participants to this study were recruited from November 8, 2012 to December 12, 2013, from one of the three trauma admitting hospitals (Middlemore, North Shore and Auckland City hospitals) in Auckland, New Zealand. The region includes urban, suburban and rural areas and has a population of approximately 1.4 million [36].

Trial eligibility criteria were (i) patients aged 16 to 69 years admitted to one of the three recruiting hospitals with an injury, (ii) screened positive for hazardous alcohol use (AUDIT score: 7-15 for females, 8-15 for males), (iii) used a mobile phone which is for their own use (i.e., not shared with another), (iv) were willing and able to read and send text messages, (v) were discharged home, (vi) were able to complete surveys in English, (vii) resided in New Zealand for the duration of the trial, and (viii) were competent and willing to provide informed consent to take part in the trial. Patients who were pregnant or whose injury was as a result of self-harm were excluded from this trial.

### Intervention

Participants in the intervention group received the active intervention through an automated system delivering one text message approximately every two days for 4 weeks (16 messages in total). Messaging was designed to commence on a Monday and finish on a Saturday with week-day messages sent at 7 pm and weekend messages at 3 pm. No specific training was provided in how to access or interpret messages. All participants were provided *The straight up guide to standard drinks* brochure [37]. This provided information about the alcohol content of different alcohol drinks as well as contact details for the Alcohol Drug Helpline, a telephone-based free and confidential service funded by the Health Promotion Agency and the Ministry of Health (www.alcoholdrughelp.org.nz).

#### Intervention development and delivery

We iteratively designed, developed, and tested the intervention using a formal process to integrate existing evidence with the input from clinical staff, patients with injury, and Māori and Pacific reference groups [35]. As part of this process, we developed a bank of SMS-text messages underpinned by BI principles and behaviour change theory. The content of messages provided participants with feedback about their drinking, encouraged contemplation about their drinking, recommended cutting down on their drinking, provided information and strategies to assist reducing alcohol consumption, and support and encouragement to aid this. The SMS text-messages used in the intervention were developed and tested in English, and translated into Te Reo Māori (the language of the indigenous people). The text message intervention had three language-based pathways for people to choose between: 1) English text messages with Te Reo Māori words of welcome and encouragement, 2) Te Reo Māori text messages, and 3) English text messages with an option to receive a greeting in Samoan, Tongan, Cook Island Māori, Niuean, Tokelauan, Tuvaluan, or Fijian. The intervention text messages have been previously published [35].

#### Comparator: Usual care

Consistent with similar trials in trauma settings and discussions with the advisory group and clinical staff, the most appropriate comparator was deemed the provision of usual care by the admitting hospital. Participants allocated to the usual care group received just one initial message: ‘Hi, thanks 4 taking part in the study. We will txt u with some questions in 3 months time’. As noted earlier, all participants received a copy of the brochure described previously. No other concomitant care was provided, and we did not specify any interventions as permitted or prohibited.

#### Procedures promoting intervention fidelity and reducing contamination

With a view to promoting engagement in the trial and as an acknowledgement of participation, participants were provided with a NZ$20 supermarket voucher at the time of recruitment. In order to ensure the intervention delivered was as close to what could be expected from a service in the field, we did not implement specific strategies to monitor adherence to the intervention.

Research assistants responsible for the recruitment of participants and trial participants were advised that not everyone will be receiving the exact same number or type of messages. In order to reduce between-group contamination, SMS text message content was stored remotely in a message bank on a secure server. An automated delivery system was used to send SMS text-messages at no cost to participants. The server and delivery system were managed by technicians with no direct contact with trial participants.

### Outcomes

#### Primary outcome measures

The primary clinical outcome is the difference in hazardous alcohol use, assessed using the pre-validated AUDIT-C [38] tool (a shorter version of the AUDIT), between intervention and control groups at 3 months. The AUDIT-C is scored on a scale of 0–12 (scores of 0 reflect no alcohol use). In men, a score of 4 or more is considered positive for problem alcohol use; in women, a score of 3 or more is considered positive. Generally, the higher the AUDIT-C score, the more likely it is that the patient’s drinking is affecting their health and safety.

#### Secondary outcomes

Self-reported data were collected on health and social outcomes and legal consequences of heavy drinking at the 12-month follow-up period using a web-based questionnaire (or telephone-based for those without web access).

Medically attended injuries during the follow-up period will be identified by probabilistic record linkage to claims lodged with the Accident Compensation Corporation (ACC: New Zealand’s national no-fault accident insurance scheme), hospital discharge and mortality databases using unique identifiers (the National Health Index number).

### Trial procedures

#### Baseline data collection

Participants were recruited from patients admitted to one of the three recruiting hospitals for an injury-related cause. All those who were potentially eligible were given information (verbal and written) about the trial. If they were interested in participating, verbal consent was gained to determine eligibility (the form used ascertained the age, gender and ethnicity of respondents) and the initial screening undertaken i.e. alcohol drinker, mobile phone user, willing to receive and send SMS messages, able to complete questionnaires in English, not pregnant, and a New Zealand resident. Written informed consent was obtained from those meeting the eligibility criteria. These people were then screened using the AUDIT tool. Trained research assistants used *The straight up guide to standard drinks* brochure [37] to assist with the AUDIT tool questions. Participants screened as having non-hazardous drinking patterns (AUDIT score <7 for females, <8 for males) were excluded from randomisation. Participants with AUDIT scores >15 indicating possible alcohol dependence were also excluded from randomisation, provided with the number of the national Alcohol Helpline and the local community alcohol and drug services, and offered referral to that service.

Research assistants were present at the hospital every day of the week during regular working hours for the duration of the recruitment period to ensure participant enrolment was maximised. In addition, members of the clinical team informed potentially eligible patients that the study was taking place and that they may be contacted by one of the research team members. Trauma coordinators based at the three hospitals would also advise the research assistants if potentially eligible patients had been admitted. Hospital case-mix reports were generated on a regular basis as a method of double checking that all potential eligible patients had been approached.

Baseline data collected from study participants included: demographic details (age, gender, ethnicity), contact details (residential address, phone numbers, email address), mobile phone details and patterns of use, cigarette and drug use, the role of alcohol in this injury, and employment and education information. Participants were then given the choice of selecting one of the three language-based pathways through which the text messages are transmitted.

In accordance with the informed consent provided by participants, research assistants extracted details pertaining to the participant’s admission from their medical record (e.g. date of injury, date and time of admission and discharge, mechanism and intent of injury, blood alcohol level, and nature of injuries).

#### Allocation - Randomisation

Individuals screening positive for hazardous drinking (AUDIT score 7-15 for females and 8-15 for males) were randomised using a secure, remote, web-based computer schedule at the time of discharge from hospital. Computer-based randomisation ensured balance for factors such as age, gender, ethnicity and recruitment hospital, and the study procedures established ensure adherence to allocation concealment.

In this single blind trial, the researchers, members of the trial Steering Committee, Clinical Reference Group, Management Committee, and the data management group (National Institute for Health Innovation [NIHI]) remained blinded to treatment allocation until the code was broken (after the last follow-up visit was completed). All baseline data collection was undertaken by research assistants who were blind to treatment allocation. Primary outcome data collection was automated and obtained via text message. Secondary outcome data were collected using an on-line survey (the latter was administered by telephone if on-line completion was not an option) or through anonymised data linkage.

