### Statistical methods

Statistical analyses of the data gathered in this trial are being performed using SAS version 9.4 (SAS Institute Inc. Cary NC). All participants considered for eligibility for the study will be accounted for in analyses. The principal evaluations of interest in this study subscribe to the ‘intention to treat’ principle, i.e. all participants are analysed in the group to which they were randomised, regardless of whether they discontinued or deviated from the protocol. However, no outcome data were collected from participants who withdrew, beyond their withdrawal day.

This trial did not include plans for interim analyses or stopping guidelines. Accordingly, analyses are being performed after 12 month follow-up has been completed. Secondary outcome data regarding subsequent injury events are expected to require a minimum of 24 months to lapse from recruitment given the time required to get cause of death information in national mortality databases. Missing data are not imputed. All statistical tests are two-tailed with a 5% significance level maintained throughout the analyses.

A CONSORT trial profile will summarise the number of participants who were considered, fulfilled eligibility criteria, reasons for exclusions, randomised, withdrawn, and lost to follow-up. Data for the intervention and control groups are being summarised with respect to baseline demographic variables (age, sex, ethnic group), employment, education, mobile phone usage, cigarette smoking, recreational drug usage, self-reported role of alcohol in the injury, mechanism of injury, nature of injury, injury intent, baseline AUDIT, and AUDIT-C mean scores.

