#### Analysis of secondary outcomes

A range of self-reported measures of alcohol-related health and social outcomes, and experience with the study, will be evaluated. The difference between the intervention and control groups will be analysed using logistic regression models for binary outcomes adjusting for the randomisation variables of age, sex, hospital centre, ethnicity, and baseline AUDIT-C score.

Differences between the intervention and control groups with respect to time to subsequent injury events (ascertained through probabilistic linkage to national databases) will be evaluated using appropriate survival analytic approaches such as Cox proportional hazards models.

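### The stated blinding rule ends with the 12-month participant follow-up and so does not cover linkage, classification and modelling of the injury outcome

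*Protocol article*

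**What the plan says.** All places are in the protocol article.

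- **Allocation - Randomisation.** The researchers, the trial committees and the data management group "remained blinded to treatment allocation until the code was broken (after the last follow-up visit was completed"). The same section describes the data linkage as anonymised.
- **Secondary outcomes.** The self-reported consequences of drinking are collected "at the 12-month follow-up period using a web-based questionnaire (or telephone-based for those without web access"). The Follow-up section describes no later contact with participants.
- **Statistical methods.** "analyses are being performed after 12 month follow-up has been completed". For injuries, "Secondary outcome data regarding subsequent injury events are expected to require a minimum of 24 months to lapse from recruitment".
- **Follow-up.** In the future tense, injury information comes from linkage to insurance claims and health ministry data at 24 months after the index admission. Routine databases are said to need roughly 24 months after an event to be complete.
- **Rationale for the intervention mode.** The current stage of the project is "collection of the final phase of secondary outcome data, and the analysis and presentation of the primary outcome data".
- **Analysis of secondary outcomes.** Time to subsequent injury "will be evaluated using appropriate survival analytic approaches such as Cox proportional hazards models".
- **Abstract, Methods/design.** "Research staff evaluating outcomes were blinded to allocation", with no restriction to particular outcomes.

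**The concern.** The code break is tied to the last participant visit, not to the last outcome dataset. Injury recurrence is one of the trial's stated hypotheses, and its data arrive after that point. The masking described for the team and the data managers has then ended, and no section extends it.

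This matters because of where the injury outcome sits in the design. The Methodological limitations section accepts that participants know their treatment, and AUDIT-C and the 12-month survey are both self-reported. Linked injury is the only hypothesised outcome that does not depend on what an unblinded participant says, so it gains most from masked handling. What remains open to influence is which probabilistic links are accepted, what counts as a subsequent injury event, and which survival model is used. If any of these is settled by people who can see the allocation and know the primary result, the comparison can be tilted and its error rate raised. The abstract's blinding statement would then claim more than the procedure delivers.

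**Working it through.** The plan gives no figure on this point, so there is none to reproduce. The check is of the order of events, followed by an illustration of size.

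**1. When the code is broken.** The sentence on blinding does not name a month. Linkage is not a visit, the last contact described is the 12-month survey, and the analyses start once 12-month follow-up is complete. Month 12 is therefore a strong inference. "Participants to this study were recruited from November 8, 2012 to December 12, 2013", so the last 12-month contact falls at 12 Dec 2013 + 12 months = about 12 Dec 2014.

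**2. When the injury data are available.** Index date + 24 months:
- first participant: 8 Nov 2012 + 24 months = 8 Nov 2014;
- last participant: 12 Dec 2013 + 24 months = 12 Dec 2015, which is 12 months after the code break in step 1.

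If events up to 12 Dec 2015 also need the stated 24 months of register lag, completeness comes at about December 2017. On either count the full linked dataset follows the code break.

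**3. How much of a 24-month window had already run.** This assumes uniform accrual over the 399 days from 8 Nov 2012 to 12 Dec 2013. At 12 Dec 2014, time since recruitment ranges from 365 to 764 days, and 24 months is 730.5 days.
- Share of participants past 24 months: (764 − 730.5) / 399 = 8.4%.
- Mean time elapsed, capped at 24 months: 0.084 × 730.5 + 0.916 × (365 + 730.5)/2 = about 563 days.
- Share of the window elapsed: 563 / 730.5 = about 77%.

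Most of the injury experience had therefore already happened. What was missing was the complete, linked dataset.

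**4. Sections side by side.** The abstract says outcome evaluators were blinded, without limit. Allocation - Randomisation ends the blind at the last visit. Follow-up and Statistical methods place the injury data later. No section says who links or classifies the injuries, or whether they hold the allocation.

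**5. Illustrative size.** Suppose k candidate definitions give null test statistics that are standard normal with common correlation ρ, and the one most favourable to the intervention is reported. The error in the favourable direction is P(max Z > 1.96), nominally 2.5%.

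| k | ρ = 0.5 | ρ = 0.7 | ρ = 0.9 |
|---|---|---|---|
| 2 | 4.5% | 4.2% | 3.5% |
| 4 | 7.8% | 6.5% | 4.7% |
| 6 | 10.4% | 8.2% | 5.4% |

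For k = 4 and ρ = 0.7, adding the small chance (0.3%) that all four are significant in the unfavourable direction gives 6.5% + 0.3% = 6.8%, against a two-sided 5%. Neither k nor ρ comes from the article; both are assumptions.

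**The case against.** The strongest reply has four parts.

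*The article does not show that anyone handling injury records knows the allocation.* This stands. The linkage is called anonymised and the abstract says evaluators were blinded. A reader might infer from the timing that linkage and classification are done unblinded, but the text gives the order of events, not what the linkage staff hold. Anonymised, in turn, speaks to identity. The article does not say that it also removes the allocation.

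*Injury events are recorded by national agencies.* This stands too. Opening the code cannot change what is recorded, and by step 3 most of a 24-month window had already passed. A reader might infer that the code was opened before any injury outcome existed, and that would be wrong. The 24 months is also explained partly as reporting lag, so the true event window may have been even more complete.

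*Event definition, link threshold and survival model belong in an SAP.* This largely stands. The SAP is not shown, and leaving the survival model open in an article is no fault in itself. Use of a unique health identifier also narrows the discretion over links. But fixing definitions in an SAP would not change the point at which the article says the code is opened.

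*The size can be exaggerated.* A reader might compute about 13% for four definitions at correlation 0.7. That is the chance that the most extreme result in either direction, harm included, crosses 1.96. It does not describe choosing the definition that favours the intervention.

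**Conclusion.** The concern holds in a limited form. As written, the blind ends with the 12-month participant follow-up, and the linked injury dataset is obtained at 24 months or later while the primary result is already being analysed. The blinding rule does not reach the handling of the injury outcome, and the abstract's general statement is not secured for it.

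The exposure is confined to link acceptance, event definition and model choice for a secondary outcome. The primary outcome is unaffected. The documents do not support saying that the injury outcome was in fact assessed unblinded, or that the definitions were still open when the code was broken. If they were open, the favourable-direction error would be about 6.5% instead of 2.5% in the illustrative case, and between 3.5% and 10.4% across the assumed grid. The conclusion rests on reading the last visit as month 12.

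**What to change.** Amend the blinding paragraph in Allocation - Randomisation so that masking of the injury outcome continues past the primary code break:

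- Run injury linkage and event classification on a file without the allocation variable.
- Sign off the source databases, event definition, time origin, horizon and survival model, and lock the injury dataset, before allocation is merged. Where an SAP already fixes these, cite it with its date relative to the code break.
- If any of them was set after the code break, say so when the injury results are reported, and limit the abstract's blinding statement to the outcomes it covers.
- In any case, reconcile the abstract with Allocation - Randomisation, Follow-up and Statistical methods on who stays masked and until when.

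The Follow-up section still describes linkage as future work, so the masked route may still be open. It costs one procedural sentence, one withheld column and a small delay before injury results are unmasked. It needs no additional data.
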